### Health economics evaluation

To assess the value for money of GP models of healthcare provision with and without VHGC we will conduct an early health economic evaluation (HEE) – in the form of a model based cost-effectiveness analysis – from the perspective of the NHS and Personal Social Services. The cost-effectiveness analysis will complement the qualitative and quantitative analyses conducted in WP1-3. The health economics (HE) team will contribute to the development of quantitative and qualitative data collection tools to be used in WP1-3. Findings from WP1 (scoping survey) and WP2 (co-design) will inform the process of: i) defining the decision problem for the early economic evaluation ii) conceptualising a decision model structure that represents the decision problem; and iii) generating a set of initial model inputs for a preliminary evaluation of the decision model. Furthermore, in preparation for a large definitive trial, the early HEE study will ascertain the feasibility of (and best practice for) collecting data – at GP practice level – on healthcare resource use (e.g. venue, staffing, consultations’ duration, set-up time, technology costs) and patient reported outcomes (e.g., health related quality of life, satisfaction) associated with the delivery of VHGCs.

Decision Model: conceptualisation and development of the decision model
^
33
^ will be guided by the NASSS domains (i.e. clinical condition, technology, value proposition, adopter system, organisation, wider system and temporal change
^
34
^ and their recent adaptation for remote consultations
^
35
^). The process of conceptualising and developing the decision model will involve decomposing and characterising discrete elements of GP models of care. The decision model will enable estimation of the value for money of a GP model of healthcare provision that includes alternative types (i.e. one-to-one, group) and modes (i.e. one-to-one, group, in-person, home, video or hybrid) of GP consultations including VHGC, compared to a GP model of healthcare provision that does not include VHGC.

Model inputs: the focus of the VHGC (e.g., diabetes annual reviews; peri and post menopause consultations) will be defined in consultation with case and comparison sites in WP3. A micro-costing analysis of VHGCs will be conducted in one of the five case sites in WP3 GP. Data on consultations (e.g. number and type of VHGCs) will be collected prospectively. The main source to estimate the unit cost of different types and modes of GP consultations will be the Unit Costs of Health and Social Care Manual (
https://www.pssru.ac.uk/unitcostsreport/). Over an up to 6-month period, all patients attending a GP consultation (any type and mode, but with the same focus as VHGCs) in one case and one comparison site will be invited to complete an online Measures of Health Benefit survey. This will include questions on utility-based health-related quality of life (i.e. EQ-5D-5L)
^
36
^, patient satisfaction (i.e. SOPS adaptation)
^
37
^ and personal details (e.g. age, weight, height).

Initial model inputs will be based on estimates of consultation costs, utility, and satisfaction. Given the limited data available to populate our decision model, and the need to make a number of expert-informed structural assumptions, we expect the results and conclusions derived from the early HEE to be subject to uncertainty. The impact of this on the decision uncertainty to consider VHGC a cost-effective addition to exiting models of GP healthcare provision will be explored using value of information analysis (VOI)
^
38
^. This methodology will enable us to identify the model parameters (and structural assumptions) considered to be the key drivers of decision uncertainty. Results from the VOI analysis will be used to inform the design of a future definitive study of a GP model of healthcare provision with VHGCs.

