We aim to recruit up to 50 patients per practice who will consent to participate in a survey questionnaire comprising patient experience, satisfaction and healthcare-related outcome components, and to allow research access to their healthcare utilisation data. The survey will be administered online and offline, immediately following VHGC attendance (through a link shared on the same platform, e.g. Microsoft Teams, or in paper format for those attending in person), and will examine both patient experiences which relate directly to VHGCs (e.g. satisfaction with care received, inclusion and access implications, quality and safety of care, need for additional follow-up, travel time saved, time off work avoided etc.) as well as to wider experiences of healthcare in the practice (e.g. satisfaction with 1:1 care, perceptions on access, quality and safety). To develop the survey questionnaire, we will draw on questionnaires piloted in our previous research on patient experiences with video consultations and group clinics. We will also adopt or adapt items from existing surveys such as the GP Patient Survey (
https://gp-patient.co.uk/) and the Primary Care Outcomes Questionnaire (PCOQ)
^
31
^. We also expect new items to be developed. The findings will be used in descriptive analyses to provide a quantitative overview of patient experience of VHGCs.

In addition to the case sites, we will recruit an equal number of comparison practices where VHGCs are not being employed (matched with case sites on location, setting, size, deprivation, QOF). As with case sites, we will aim to recruit 50 patients from each comparison site with recruitment targeted at similar patients as those taking part in VHGCs in terms of age, gender and chronic conditions treated. They will receive a shorter version of the patient survey used in case sites with questions relating only to wider experiences of healthcare at their practice and will be asked to consent to research access to their healthcare utilisation data. Our team will also provide support to any comparison or case sites who choose to administer the Patient Activation Measure (PAM) in the context of local service improvement.

**
*iii. Impact of VHCGs on healthcare utilisation*
**

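### The survey supplying the decision model's utility and satisfaction inputs has no stated offline route, so digitally excluded patients are likely to be under-represented in inputs meant to cover all attenders

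*Protocol article*

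**What the plan says.** Under Health economics evaluation (Model inputs), over a period of up to six months, the target is "all patients attending a GP consultation (any type and mode, but with the same focus as VHGCs) in one case and one comparison site". These patients "will be invited to complete an online Measures of Health Benefit survey". The survey holds the EQ-5D-5L, an adapted satisfaction scale and personal details. Its results go into the model: "Initial model inputs will be based on estimates of consultation costs, utility, and satisfaction". The same section describes a comparison between a model of GP care that may contain several types and "modes (i.e. one-to-one, group, in-person, home, video or hybrid) of GP consultations including VHGC" and a model without VHGC. It also gives the early evaluation a feasibility task: to learn whether, and how best, resource-use and patient-reported data can be gathered at practice level before a definitive trial.

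Under Quantitative methods (subsection ii), the case-site patient survey is handled differently: "The survey will be administered online and offline, immediately following VHGC attendance", with a link for those on the platform and the form "in paper format for those attending in person". For comparison sites that subsection mentions a shorter version and states no route.

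Digital exclusion is treated as important elsewhere. It is given as a reason why some patients cannot attend VHGCs (Qualitative methods, subsection i), as a reason for individual interviews in person or by phone (WP2), and as one of the theoretical threads (Data synthesis and engagement with theory).

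**The concern.** The article fixes the response route for this survey and names only one. A patient who joined a consultation by video has shown that they can get online. A patient who came in person or spoke by telephone need not be able to. The chance of answering can therefore vary with consultation mode, and the patients missed are those whom the rest of the study takes care to include.

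Two things are at stake. First, the target is all attenders and the model compares whole ways of running GP care, which also serve people who are not online. Utility and satisfaction inputs taken only from people able to answer online may not describe that population. Second, an online survey cannot show whether patients who are not online can be reached, which is part of what the feasibility task needs to establish. Value of information analysis, as described, expresses uncertainty in the inputs it is given; it does not repair selective coverage of those inputs.

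**Working it through.** The article states no sample size, response rate or utility value for this survey, so there is no figure to reproduce. What follows is an identity with assumed inputs.

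**1. Effect on the mean of one mode.** Among attenders of a mode, let p be the share unable to answer online, U the mean utility of those who can, and U − D the mean of those who cannot. Suppose everyone able to answer does so.

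- Mean of all attenders: (1 − p)U + p(U − D) = U − pD.
- Mean seen in an online survey: U.
- Overstatement relative to all attenders: pD.

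For video attenders p = 0, so the overstatement is 0. For in-person attenders, with p from 0.05 to 0.30 and D from 0.05 to 0.20 (assumed):

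| p | D = 0.05 | D = 0.10 | D = 0.20 |
|---|---|---|---|
| 0.05 | 0.0025 | 0.005 | 0.010 |
| 0.10 | 0.005 | 0.010 | 0.020 |
| 0.20 | 0.010 | 0.020 | 0.040 |
| 0.30 | 0.015 | 0.030 | 0.060 |

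If D = 0 there is no effect; if D is negative the sign reverses. The groups named in the co-design section (sight loss, hearing loss, learning difficulties) make a positive D plausible, but nothing in the article quantifies it.

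**2. Hybrid groups.** If a share h of VHGC patients attend in person with the same p and D, the VHGC mean is overstated by hpD. The difference in overstatement between modes is pD(1 − h). At p = 0.20 and D = 0.10:

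- h = 0: 0.020
- h = 0.25: 0.020 × 0.75 = 0.015
- h = 0.50: 0.020 × 0.50 = 0.010

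**3. In-person care in both models.** The model with VHGC can also contain one-to-one and in-person care. If fixed mode-specific means are used and a share s of in-person consultations moves to VHGC, the net difference between the models is s × pD(1− h), which cannot exceed pD. If instead only patients able to go online move, the in-person patients left behind have p/(1 − s) unable to answer. The error in the VHGC model is then (1 − s) × [p/(1 − s)] × D = pD, the same as in the model without VHGC, and the two cancel. The article does not say how the inputs will be applied, so the net effect lies anywhere from nil up to pD under these assumptions.

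**4. What an online survey does to the mode contrast.** Suppose mode has no effect on utility and those able to go online have mean U in every mode. The planned survey shows U − U = 0, which is correct. Adding offline respondents makes the in-person mean U − pD. A crude contrast then favours VHGC by U − (U − pD) = pD, or 0.020 at p = 0.20 and D = 0.10. All of that is case mix.

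**The case against.** A reader might infer that the online form biases the comparison of consultation modes in favour of in-person care, by about pD. The documents do not support that. As step 4 shows, comparing in-person patients who can go online with video patients is nearer to like-for-like, and adding offline patients to an unadjusted contrast could bring in a case-mix difference. The in-person mean is overstated only against the mean of all in-person attenders. Hybrid attendance and in-person care within both models reduce any net effect further. The clinical focus is not yet fixed, so p could be very small, and both the size and the sign of D are assumptions. This part of the objection stands.

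It can also be said that the article writes online, not online only, and that a paper or assisted option may sit in a fuller document. That is possible. But this is more than a detail left out: the article commits to a route here, and where an offline route was intended for the other survey it says so. If an option exists, one sentence settles the matter. The precedent is limited, since the offline wording in that survey is tied to VHGC attendance at case sites.

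Finally, the evaluation is described as early, with limited data and uncertain conclusions. That lowers the consequence for any cost-effectiveness claim. It does not answer the feasibility point, because learning how to collect patient-reported outcomes is one of the stated aims.

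**Conclusion.** The point holds as a coverage defect. The survey is meant for all attenders, but as written it would under-represent those who cannot answer online, mainly in-person and telephone attenders. The utility and satisfaction inputs may therefore not represent the population served by the care models, and the feasibility aim is only partly met.

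Under the assumed ranges, the in-person mean utility would be 0.0025 to 0.06 above the mean for all in-person attenders. That range rests wholly on assumed p and D, on full response among those able to answer, and on D being positive. It is not an estimate of bias in the cost-effectiveness result, whose size and direction are unknown. Any such effect shrinks where hybrid patients attend in person or where both models contain in-person care, and it may vanish.

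**What to change.** - Offer the Measures of Health Benefit survey on paper or by telephone alongside the online form, at both sites.
- Record the response route and the consultation mode for each respondent.
- Report response rates and respondent characteristics by consultation mode.
- Present the utility inputs twice: for all respondents, to describe the population served, and for respondents able to answer online, as the nearer like-for-like contrast. Adjust both for patient characteristics such as age.
- Do not adjust the mode contrast for response route. All-video groups contain no patients who can answer only offline, so that adjustment would largely return the comparison to online respondents and undo the gain in coverage.

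The cost is a small clerical load for forms, calls and data entry at two sites over up to six months, and a mix of response routes that has to be reported. If an offline option already exists, a sentence saying so is enough for the first item.

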### Data synthesis and engagement with theory

We are using the Non-adoption, Abandonment and Challenges to Spread, Scale-Up and Sustainability (NASSS) framework to inform study design and data collection on the multiple interacting influences affecting implementation and sustainment of VHGCs
^
34
^. The framework will also contribute in crafting narrative case studies combining qualitative, quantitative and cost-related data for each site where VHGCs have been taking place. Integration of qualitative and quantitative data will inform the development of a theory of change, i.e. set of assumptions on successful delivery of VHGCs and un/anticipated implications in practice. Extending previous research on in-person and video group consulting
^
26,
27
^, we will draw on a number of theoretical threads from science and technology studies, medical sociology and organisational theory to underpin data analysis and synthesis. This includes theory on: a) burden of treatment and patient ‘work’ related to the responsibilities placed on patients in the context of group consultations
^
38
^, b) digital exclusion and intersectionality around multiple dimensions that contribute to some people being served less well by remote means of group-based care
^
39,
40
^, c) health service complexity including a departure from linear cause-effect relationships to recognising interdependence and emergence in group-based care delivery
^
41,
42
^ and d) experiential knowledge mobilised to support clinical care
^
10,
12
^.

## Ethics and governance

Approval has been granted by the London Hampstead Research Ethics Committee and UK Health Research Authority, reference number 22/PR/0277 (19 May 2022), and subsequent amendments. The study is overseen by an independent external advisory group with a lay chair and diverse representation from policy, clinical care, the commercial sector, and people with experience on patient advocacy groups or regulatory bodies.

## Outputs and dissemination

We plan a number of key outputs including: a) empirical academic articles and conference presentations, b) co-designed guidance for patients and service providers on developing effective and inclusive video and hybrid group consulting, c) policy briefings around supporting equitable group-based digital services. We will facilitate knowledge sharing and capacity building across participating sites through joint co-design sessions, learning reports, and virtual learning events to share formative and summative evaluation findings and drive local improvement.

## Conclusions

We aim to develop transferable learning on sociotechnical change in healthcare, using VHGCs as an exemplar of technology-supported innovation. Findings will inform policy and practice, as well as the design of a future definitive study.

## Data Availability

No data are associated with this article.
